## Abstract

**Background:**

Stress urinary incontinence (SUI) is a common source of distress among women during and after pregnancy. It has a negative effect on quality of life but with poor care-seeking. Mobile health (mHealth) may be a promising solution with potential advantages. However, there is uncertainty whether a mobile app is effective for SUI symptom improvement during and after pregnancy. The implementation is also unclear. We developed an app named UIW (Urinary Incontinence for Women) aimed at improving perinatal incontinence.

**Objective:**

The objective of this study is to evaluate the effectiveness of the UIW app-based intervention in improving SUI symptoms among pregnant women and explore the facilitators and barriers to using the UIW app to help refine and optimize the intervention.

**Methods:**

This study is a hybrid effectiveness-implementation trial with a randomized controlled trial alongside a mixed-methods process evaluation according to the Reach, Effectiveness, Adoption, Implementation, and Maintenance (RE-AIM) framework. Pregnant women with SUI (n=336) will be recruited from a university-affiliated hospital in China. They will be randomly allocated (1:1) to either the intervention group that receive usual care plus UIW app or control group that receive usual care alone. The intervention period will last 2 months. The 5 dimensions of the RE-AIM framework will be evaluated at recruitment (-T1), baseline (T0), immediately after intervention (T1), 42 days after delivery (T2), 3 months after delivery (T3), and 6 months after delivery (T4) through project documents, online questionnaires and a pelvic floor muscle training diary, surface electromyography, log data in the background management system, and qualitative interviews. Data analysis will follow the intention-to-treat principle. Descriptive statistics, *t* tests, chi-square tests, and a linear mixed model will be used to analyze the quantitative data. Deductive and inductive content analysis will be used to analyze the qualitative data.

**Results:**

The effectiveness-implementation trial started in June 2020, trial recruitment was completed in October 2020, and the intervention will last for a 2-month period. Completion of the 6-month follow-up will be in July 2021, and we anticipate that the results of this study will be published in December 2021.

**Conclusions:**

This study will evaluate both effectiveness and implementation of the UIW app-based intervention among pregnant women. The hybrid effectiveness-implementation trial design according to the RE-AIM framework with a mixed-methods approach will give valuable insights into the effects as well as facilitators and barriers to the implementation that will influence the effects of the UIW app-based intervention.

**Trial Registration:**

Chinese Clinical Trial Registry ChiCTR1800016171; http://www.chictr.org.cn/showproj.aspx?proj=27455

**International Registered Report Identifier (IRRID):**

PRR1-10.2196/22771

## Introduction

### Background

Stress urinary incontinence (SUI) is the most prevalent type of urinary incontinence (UI) accounting for half of women suffering from UI [1,2]. SUI is defined as the complaint of involuntary urine leakage on effort or physical exertion (eg, sports activities) or during sneezing or coughing [3]. Pregnancy and childbirth are regarded as the major predisposing factors of SUI [4]. About 40% of women experience SUI during pregnancy [5], and the prevalence of SUI after delivery is over one-fifth of women [6]. Other types include urgency UI, which is characterized by involuntary urine leakage with a strong desire to urinate, and mixed urinary incontinence, which is the combination of SUI and urgency UI [7]. UI negatively affects women’s activities of daily life, mental well-being, and quality of life [8-10].

Pelvic floor muscle training (PFMT) is the first-line therapy for SUI, and the National Institute for Health and Care Excellence recommends women perform PFMT, especially during pregnancy [11]. Despite the availability of this effective therapeutic option for SUI, less than 30% of women seek help from health care professionals [12,13]. The reasons for not seeking treatment are multifaceted, such as embarrassment, stigma, insufficient knowledge, and perception of SUI among pregnant women [14]. Besides, a shortage of obstetric health care professionals and time restrictions during appointments also impede the delivery of perinatal incontinence care [15]. Given the unoptimistic condition, effective strategies are urgently needed to overcome these barriers. With the rapidly evolving development of information and communication technologies, mobile health (mHealth) may be a novel and promising strategy to improve perinatal SUI care [16].

mHealth is defined as achieving health objectives using mobile devices, such as mobile phones and other wireless devices [17]. With the advantages of anonymity, convenience, flexibility, and information support of mHealth, barriers to delivering perinatal incontinence care are lowered [18]. Women feel like they have greater privacy, are less embarrassed, have greater self-awareness of SUI, and appreciate the easy access to treatment options for SUI [19,20]. Moreover, 89% of the Chinese population use mobile phones, with a high prevalence of mobile internet usage in 2019 [21]. Thus, mHealth offers enormous potential to deliver SUI care to women on account of its advantages and high accessibility [16].

Several studies have proven mHealth to be effective for SUI management among community-dwelling women [22,23]. However, studies investigating the utility for mHealth to improve SUI symptoms during and after pregnancy are scarce [24]. Only one study was conducted with primiparas women [25]. Regretfully, it showed no significant difference in SUI symptoms between the mobile app–based intervention group and control group, and the reasons for the less-than-optimistic results were underexplained. The most recent Cochrane systematic review also revealed that the effect of antenatal PFMT as a treatment for UI in incontinent women is uncertain [26], which arose from poor reporting of the control arm and process details in the study [27]. Moreover, pregnant women’s use patterns and facilitators and barriers to using the app, referred to as process evaluation, should be explored further, which may explain variations in the success of mHealth interventions [28,29].

We developed a mobile app named UIW (Urinary Incontinence for Women) through an iterative and user-centered approach targeting pregnant women to improve perinatal incontinence care. It is an evidence-based and theory-driven app containing multiple intervention components based on the input of important stakeholders’ perspectives (pregnant women, obstetricians, and nurses). Therefore, we will assess the effectiveness and implementation of the UIW app, as adopted by pregnant women, compared to usual care, in this study, using a hybrid effectiveness-implementation study design through mixed-methods research [30,31]. The results of this study will also contribute to updating the Cochrane review to determine the effect of antenatal PFMT as a treatment for UI.

### Objectives

The overall goal of this effectiveness-implementation study is to provide more valuable insights into underlying reasons for the effective or ineffective results of app-based interventions among pregnant women with SUI compared to usual care. Then, it will provide a possibility to foster the implementation of an app-based intervention to improve incontinence care during and after pregnancy. There are 2 specific objectives in this study. First, we will evaluate whether the UIW app-based intervention is effective in improving SUI symptoms of pregnant women, as compared to usual care. Second, we will explore the facilitators and barriers to using the app during the implementation to help refine and optimize the intervention.

## Methods

### Study Design

This study is a hybrid type 1 effectiveness-implementation trial due to the need to determine the effectiveness of the UIW app-based intervention and understand the implementation to explain the effects of the intervention [30,31]. A randomized controlled trial (RCT) was designed to evaluate the effectiveness of the UIW app-based intervention compared to usual care among pregnant women with SUI, in parallel with an implementation research through a mixed-methods process evaluation following the explanatory sequential mixed-methods design (Figure 1) [32,33]. Reach, Effectiveness, Adoption, Implementation and Maintenance (RE-AIM) framework will be used to guide the evaluation, which is the vital evaluation theory on health promotion intervention [34,35].

This trial protocol has been developed in line with the Consolidated Standards of Reporting Trials of Electronic and Mobile HEalth Applications and onLine TeleHealth (CONSORT-EHEALTH) guidelines (Multimedia Appendix 1) [36], Standard Protocol Items for Randomized Trials (SPIRIT) 2013 statement (Multimedia Appendix 2) [37], and guidance for the qualitative research undertaken with the trial (Multimedia Appendix 3) [38]. The CONSORT flowchart is displayed in Figure 2.

**Figure 1 figure1:**
[figure not shown]
An overview of the trial design for the UIW (Urinary Incontinence for Women) app trial. PFMT: pelvic floor muscle training; RE-AIM: Reach, Effectiveness, Adoption, Implementation, and Maintenance; sEMG: surface electromyography; -T1: recruitment period; T0: baseline; T1: immediately after intervention; T2: 42 days after delivery; T3: 3 months after delivery; T4: 6 months after delivery.

**Figure 2 figure2:**
[figure not shown]
Trial flowchart according to CONSORT (Consolidated Standards of Reporting Trials). BPMSES: Broome Pelvic Muscle Self-Efficacy Scale; ICIQ-UI-SF: International Consultation on Incontinence Questionnaire-Urinary Incontinence Short Form; IIQ-7: Incontinence Impact Questionnaire-7; UIW: Urinary Incontinence for Women; T1: immediately after intervention; T2: 42 days after delivery; T3: 3 months after delivery; T4: 6 months after delivery .

### Setting

The study will be conducted in Shenzhen Hospital, Southern Medical University, a university-affiliated, tertiary level-A, public hospital in China. An average of 2000 pregnant women per month receive routine antenatal assessments in the hospital, and a vast majority of these pregnant women have access to a mobile phone and the internet [21].

### Eligibility of Participants

#### Inclusion Criteria

Pregnant women will be eligible if they are at least 18 years of age, have a singleton pregnancy according to ultrasonographic evaluation, are at 24-28 gestational weeks, have access to a mobile phone and the internet, and have SUI symptoms with ≥1 leakage episodes over the past 4 weeks (SUI symptoms are assessed by asking the question “When does urine leak?”). The question is an unscored item in the International Consultation on Incontinence Questionnaire-Urinary Incontinence Short Form (ICIQ-UI-SF), which has good reliability and validity [39]. SUI is defined as involuntary urine leakage on effort or physical exertion (eg, sports activities) or during sneezing or coughing [3]).

#### Exclusion Criteria

Pregnant women will be excluded if they have a psychiatric illness or cognitive impairment; previous UI; pelvic organ prolapse or pelvic surgery; or serious comorbidities or complications like heart disease, diabetes mellitus, hypertensive disorder of pregnancy, threatened abortion, placenta previa, placental abruption and premature rupture of membranes, fetal growth restriction, and amniotic fluid abnormalities.

### Intervention

#### UIW App

The UIW app is a mobile app for Chinese pregnant women with SUI developed by a research team from Shenzhen Hospital, Southern Medical University with technical assistance from the Guangdong Zhuoshang Network Technology Company (Registration Number: 2019SR1342273). There are 4 major modules in the UIW app including the Risk Assessment forum, Health Knowledge forum, PFMT forum, and Online Evaluation forum, with the functions of education, reminders, self-monitoring, and others, all arising from behavior change techniques (Multimedia Appendix 4) [40]. The 4 modules are visibly placed on the home page of the UIW app (Figure 3).

**Figure 3 figure3:**
[figure not shown]
Screenshots of the UIW (Urinary Incontinence for Women) app, including the (A) Home Page, (B) Risk Assessment forum, (C) Health Education forum, (D) Pelvic Floor Muscle Training (PFMT) forum, and (E) Online Evaluation forum.

The Risk Assessment forum provides a risk prediction for SUI during the early stage of pregnancy based on a predictive tool previously developed by the research team [41]. According to the pregnant woman’s clinical risk factors, it identifies the high-risk population and gives feedback to the users whether they are at a high or low risk level.

The Health Education forum provides 5 topics specific to SUI and general pregnancy care, including SUI and lifestyle factors associated with SUI (weight management and constipation prevention [42,43], pelvic floor muscle care, and general antenatal care). A literature review, user needs analysis, and multidisciplinary expert group meeting were carried out to create the 5 topics.

The PFMT forum provides a personalized and instructional PFMT protocol adapted from the “Tät-an internet-based intervention providing PFMT to treat SUI” [44]. The PFMT is ordered by increasing difficulty. It consists of 2 basic levels and 4 advanced levels including different combinations and repetitions of 4 commonly used contraction types: test contraction, strength contraction, endurance contraction, quick contraction. When performing PFMT, the app shows real-time, dynamic guidance in the form of columnar graphics that present the duration and intensity of pelvic floor muscle contraction with concomitant relaxation. Pregnant women follow the image and sound command to contract and relax the pelvic floor muscles. Alarms can also be set to push notifications reminding the pregnant women to train.

The Online Evaluation forum provides reliable and validated questionnaires to evaluate the women’s SUI severity, quality of life, and self-efficacy with PFMT.

Additionally, at the bottom of the home page, there are other functions including recording of behaviors in daily life, consulting health care professionals about SUI-related questions, watching videos related to SUI, managing personal information, and system setup. Driven by administrative and adherence-focused guidance, the app also provides technical support, adherence monitoring, and reminders sent by the background management system in case the UIW is not logged into within 7 days [45]. The intervention period will last 2 months because research evidence indicates that 8 weeks PFMT is enough to improve the symptoms of SUI [46]. During the intervention period, pregnant women will autonomously use the app; it is up to them to determine their usage pattern in terms of frequency and duration of use.

The researcher will assist pregnant women in the intervention group with downloading the UIW app, registering, and installing their accounts. The pregnant women will be free to set up their usernames and passwords to submit the account application. Once the researcher confirms submission through the background management system, their accounts will be activated. The pregnant women will need to complete their personal information. Participants will be informed that the researchers have access to their profile.

A link to the electronic user manual and instructions for the UIW app will be fixedly displayed at the top of the home page. Technical support can be provided via the user manual and instructions on how to operate the UIW app. Moreover, the pregnant women can post their technology-related questions through the Assistance and Feedback function below the System Setup module. The researcher will respond to them within 24 hours.

#### Usual Care

The pregnant women in the intervention group and control group will both receive the same usual care. Usual care involves one-to-one health education about SUI and PFMT practice guidance at the time of recruitment by experienced obstetricians. It is delivered based on the Guidelines on the Medical Service Capacity of Tertiary Obstetrics and Gynecology Hospitals (National Health Commission of the People’s Republic of China, 2017 edition) [47]. The health education is verbally provided, which covers information corresponding to the 5 topics in the Health Education forum of the UIW app. PFMT practice guidance is teaching the correct pelvic floor muscle contraction technique and confirmation by obstetricians of a correct contraction through perineum palpation with the pregnant women in the supine position. Women will be directed to be aware of the feeling of selectively contracting muscles surrounding the urethra, vagina, and anus while relaxing the abdomen and buttocks muscles. Meanwhile, obstetricians will put one hand on the perineal body and the other hand on the abdomen to identify if women can correctly contract and relax the pelvic floor muscles; participants will be encouraged to contract the pelvic floor muscles more than 100 times per day [26].

### Measurements and Instruments of Data Collection

#### Overview

We will use a mixed-methods approach to evaluate the effectiveness and implementation of the trial according to the RE-AIM framework. Quantitative methods will be specifically used to measure the dimensions of Reach, Effectiveness, Adoption (UIW app usage results and patterns), Implementation, and Maintenance. For the Adoption dimension, qualitative methods will be used to explore the facilitators and barriers to adoption of the UIW app-based intervention from the pregnant women’s perspective. Multimedia Appendix 5 demonstrates the measures used in this study. Data will be collected at recruitment (–T1), baseline (T0), immediately after the intervention (T1), 42 days after delivery (T2), 3 months after delivery (T3), and 6 months after delivery (T4). Data will be collected from both the UIW app-based intervention group and control group. For the Reach dimension, the participation rate of eligible pregnant women will be examined using the project document data recorded by the researchers. For the Effectiveness dimension, there is 1 primary outcome, and there are 4 secondary outcomes, which are described in the following sections.

#### Primary Outcome

Symptoms of SUI will be evaluated using the ICIQ-UI-SF [48]. The ICIQ-UI-SF is a 4-item instrument with 3 scored items assessing the frequency of leakage, amount of leakage, and overall impact of leakage on life and 1 unscored item diagnosing the type of UI. The total score ranges from 0 to 21, with 0-7 indicating mild symptoms, 8-13 indicating moderate symptoms, and 14-21 indicating severe symptoms. The Chinese version of the ICIQ-UI-SF has a Cronbach α coefficient of 0.71 and over 95% agreement between the 2 tests [49].

#### Secondary Outcomes

The secondary outcomes include pelvic floor muscle strength, quality of life, self-efficacy with PFMT, and risk factors for SUI.

Pelvic floor muscle strength will be assessed using sEMG with the Vishee neuro-muscle stimulator (MyoTrac Infiniti, model SA9800, Thought Technology Ltd, Montreal, Quebec) [50]. It will be performed by following the Glazer protocol by 2 independent and experienced obstetricians who have passed the medical qualification examination and have more than 5 years of working experience. After participants are in a supine lithotomy position, a drop-shaped vaginal probe (registration certificate number: 20152211142, type VET-A, produced by Nanjing Vishee Medical Technology Ltd, Nanjing China) will be placed into the vagina. Participants will be instructed how to correctly contract the pelvic floor muscles to avoid crosstalk contamination of the surrounding muscles before starting the test. Then, participants will follow the text hints and voice prompts of the automated protocol software to contract and relax the pelvic floor muscles. The whole test includes 5 indicators of amplitude (µV): pretest resting, phasic contraction, tonic contraction, endurance contraction, and posttest resting. A lower amplitude indicates weaker pelvic muscle strength. sEMG is a reliable way to measure pelvic floor muscle strength, and its values are closely related to SUI [51].

Quality of life among pregnant women with SUI will be assessed using the Incontinence Impact Questionnaire-7 (IIQ-7) [52]. The IIQ-7 is a 7-item instrument with 4 domains including physical activity, travel, social activities, and emotional health. Higher total score indicates a higher level of impact on life. The Chinese version of the IIQ-7 has a Cronbach α coefficient of 0.824 and high construct validity [53].

Self-efficacy with PFMT will be measured using the Broome Pelvic Muscle Self-Efficacy Scale (BPMSES) [54]. The BPMSES is a 23-item instrument with 14 items in the dimension of self-efficacy expectations and 9 items in the dimension of outcome expectations. A total score of 0-33 indicates low self-efficacy, 34-66 indicates moderate self-efficacy, and 66-100 indicates high self-efficacy. The Chinese version of the BPMSES has a Cronbach α coefficient of 0.912 and a test-retest reliability coefficient of 0.910 [55].

Risk factors for SUI among pregnant women will be assessed using a self-designed questionnaire, investigating weight, condition of constipation, active and passive smoking, and consumption of liquids containing caffeine.

For the dimension of Adoption, the pregnant women’s PFMT adherence and activity in the 2 groups, usage results and patterns of use of the UIW app for the intervention group, other possible apps and websites used by the control group, and facilitators and barriers to adoption of the app will be explored through quantitative and qualitative methods. PFMT adherence and activity as well as usage results and patterns will be evaluated using quantitative methods through the log data of the background management system for the intervention group; a self-administered, electronic PFMT diary; and an electronic questionnaire (Multimedia Appendix 5). For the qualitative interviews, we will adopt a purposive sampling strategy to select women from the 2 groups based on the primary outcome of the SUI symptom score at the end of the intervention. Pregnant women will be selected at a ratio of 1:1 in the higher and lower scores until achieving data saturation such that no new themes emerge during data analysis. The interviews will be performed by a researcher ([name]) via telephone or face-to-face. The interviewer is a female nurse with a master’s degree in nursing science and formal training in qualitative studies. A semistructured interview guide was developed by the research team and covers the topics of user experiences, preferences, and expectations (Multimedia Appendix 5). Data collection, management, and analysis will be carried out concurrently, which makes it possible to adapt and refine the interview guide [56]. All interviews were audiotaped after gaining permission from the participants.

For the dimension of Implementation, the fidelity of the intervention and usual care provided will be evaluated (Multimedia Appendix 5).

For the dimension of Maintenance, the measures used to assess “Effectiveness,” “Adoption,” and “Implementation” will be repeatedly assessed in the follow-up period at the T2, T3, and T4 time points.

### Data Management and Analysis

#### Quantitative Data

To avoid bias due to unnecessary face-to-face contact, data for pregnant women in both the intervention group and control group are collected electronically, using app-based and internet-based methods, respectively. After the data are exported from the app’s background management system and questionnaire website, data will be entered directly in a special database for the UIW app and saved in the database by researchers on a password-protected computer. Each participant is identified by a unique study ID assigned by the independent researcher assistant at the time of recruitment. And the “log” connecting the participants with the study IDs is held by the independent research assistant.

SPSS (version 25.0; IBM Corp, Armonk, NY) will be used for all quantitative data analysis. Descriptive statistics will be used to show continuous variables as mean (SD) and categorical variables as frequency and percentage. The baseline data will be compared between the intervention and control groups as well as between participants completing the follow-up of this study and those who drop out, with the independent sample *t* test for continuous variables and the chi-square test or Fisher exact test for categorical variables. The effects of the intervention within each group will be assessed with a paired *t* test for the severity of SUI, quality of life, and self-efficacy with PFMT and a McNemar chi-square test for risk factors. To compare the effects of the intervention between groups for the repeated measures, including severity of SUI, quality of life, and self-efficacy with PFMT, a linear mixed model will be used, which allows for missing data [57]. The model will include subjects as random effects and time, intervention, and the interaction between intervention and time as fixed effects. Pelvic floor muscle strength will be compared between groups using an independent sample *t* test. For the risk factors and PFMT adherence, chi-square tests will used to compare the differences between groups. *P* values <.05 will be considered statistically significant.

Participants with missing data will also be included in the analysis following the principle of intention-to-treat analysis. Missing data at follow-up will be replaced with the corresponding values at baseline.

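### Before-after tests within each arm are labelled effects of the intervention; they should be reported as descriptive change, with effectiveness tied to the between-group contrast

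*Protocol article*

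**What the plan says.** The protocol article, Quantitative Data, plans two sets of analyses for the same outcomes.

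- **Within each arm.** "The effects of the intervention within each group will be assessed with a paired" t test for symptom severity (the primary outcome), quality of life and self-efficacy. Risk factors get a McNemar test.
- **Between arms.** A linear mixed model is planned, with this purpose: "To compare the effects of the intervention between groups for the repeated measures, including severity of SUI, quality of life, and self-efficacy with PFMT". Its terms are listed as "time, intervention, and the interaction between intervention and time as fixed effects". For the binary outcomes: "For the risk factors and PFMT adherence, chi-square tests will used to compare the differences between groups".

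One threshold, P<.05, serves all of them. No sentence ranks the two sets or calls the first descriptive.

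Under Usual Care: "The pregnant women in the intervention group and control group will both receive the same usual care". That care is not passive: "Usual care involves one-to-one health education about SUI and PFMT practice guidance at the time of recruitment by experienced obstetricians". The Objectives section frames effectiveness relative to usual care.

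**The concern.** A before-after test answers whether scores in that arm moved. It cannot say why. In the control arm there is no app for the change to be an effect of. In the app arm, the change adds any app effect to everything that both arms share.

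The shared part is unlikely to be zero. All women are taught PFMT at recruitment, pregnancy advances, and the three later visits follow delivery. Entry requires recent leakage, which invites regression to the mean. The Background puts SUI at about 40% of women in pregnancy and says that "the prevalence of SUI after delivery is over one-fifth of women" affected. These are population figures and give no within-woman change, but they make change unrelated to the app plausible.

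At stake is the wording of the result for the primary outcome. Once a within-arm P value has been named an intervention effect in advance, a report could cite a significant change in the app arm as evidence of effectiveness even if the randomized comparison is null. Contrasting a significant arm with a non-significant one is not a comparison of the arms.

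**Working it through.** **1. The plan's own figure.** Inputs from Sample Size Calculation: effect size 0.344, two-sided .05, power 0.80, attrition 20%.

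- Normal approximation: n per arm = 2(1.960 + 0.842)² / 0.344² = 132.7, so 133 per arm and 266 in total.
- Exact t test: 133.6, so 134 per arm and 268 in total, as stated.
- Attrition: 134 / 0.8 = 167.5, so 168 per arm and 336 in total, as stated.

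The trial is therefore sized as a comparison of two independent groups, not for before-after tests.

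**2. What each test addresses.** Let *a* be the app effect and *s* the sum of the shared components (taught PFMT, time, delivery, regression to the mean).

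- Paired test, app arm: tests *a* + *s* = 0.
- Paired test, control arm: tests *s* = 0.
- Between-group contrast: (*a* + *s*) − *s* = *a*.

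Only the third isolates *a*. Delivery does not enter every visit. Entry at 24-28 weeks plus 2 months puts T1 at about 32 to 37 weeks, so the T0-T1 change mostly reflects advancing pregnancy and taught PFMT. Delivery enters at T2 to T4.

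**3. Number of paired tests.** The article does not say which visits are paired. With T0-T1 only, there are 3 scales × 2 arms = 6. With every follow-up visit paired with baseline, there are 3 × 4 × 2 = 24. McNemar tests come on top in either case.

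**4. Illustration with no app effect.** The documents give no natural change, so an equal change *d* in both arms is assumed, in units of the SD of change. (If baseline and follow-up correlate at 0.5, this equals the SD of the score, since √(2(1 − 0.5)) = 1.) The chance *p* that one arm is significant is the chance that a noncentral t with 133 degrees of freedom and noncentrality *d*√134 exceeds 1.98 in absolute value. The arms are independent, so significance in the app arm only has probability *p*(1 − *p*).

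| *d* | *d*√134 | *p*, one arm | App arm only | Both arms |
|---|---|---|---|---|
| 0.1 | 1.16 | 0.210 | 0.166 | 0.044 |
| 0.15 | 1.74 | 0.407 | 0.241 | 0.165 |
| 0.2 | 2.32 | 0.633 | 0.232 | 0.400 |
| 0.25 | 2.89 | 0.819 | 0.148 | 0.671 |
| 0.3 | 3.47 | 0.932 | 0.064 | 0.868 |
| 0.5 | 5.79 | >0.99 | about 0 | >0.99 |

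With all 168 per arm, the app-only column becomes 0.188, 0.250, 0.196, 0.093, 0.028 and about 0. A between-arm test of one contrast keeps its 5% error rate throughout. If the shared change is a worsening, the misleading pattern is worsening in controls only, with the same probability by symmetry.

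**The case against.** The strongest reply is that the within-arm tests are not the basis of inference. The effectiveness objective is comparative, the sample size is a two-group calculation, and the sentences that follow plan a between-group model with an intervention-by-time term, plus between-group chi-square tests for risk factors. This stands. A reader might infer that natural change will be reported as an app effect, but no section says that effectiveness will be concluded from the paired tests. They are also run in both arms, so a shared change would tend to show in the controls as well.

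Two larger numbers are also tempting and should not be used. Counting trials in which exactly one arm is significant gives 2*p*(1 − *p*) = 46% at 0.2 SD, but that includes trials in which only the control arm is significant; the app-only figure is half of it. Reading 24 paired tests as a minimum goes beyond the text.

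It can also be said that intervention here means whatever care each arm received, and that rules of interpretation belong in the analysis plan, which is not shown. The first does not help: a before-after change is not the effect of usual care either, since time and regression to the mean are still in it. On the second, the point is not a missing rule but a label that the article states, and states wrongly, for its primary outcome.

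**Conclusion.** The concern holds as a mislabelled and redundant analysis that carries a risk of misreading. It is not a fault in the randomized comparison. The within-arm tests do not measure an effect of the app in either arm, yet they are named as effects, cover the primary outcome and share the significance threshold of the mixed model.

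The size of the risk depends on a shared change that the documents do not give. For one scale at one visit, with 134 per arm and no app effect, the false app-only pattern has a probability of about 15% to 24% for shared changes of 0.1 to 0.25 SD. It falls to 6% at 0.3 SD and to almost nothing at 0.5 SD. At larger changes both arms are significant, and the label would then call both changes intervention effects. The sample size and the error rate of the between-group contrast are unaffected. Correction is worthwhile because it closes a stated route to a false effectiveness claim.

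**What to change.** In the Quantitative Data section, or in the analysis plan before results are reported:

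1. Rename the within-arm results as change from baseline within each group.
2. Report them descriptively: mean change with 95% confidence interval from the planned mixed model for the three scales, and proportions at each visit for the risk factors. Do not present paired t or McNemar P values as tests of effect.
3. Say which visits are compared with baseline.
4. Add one sentence stating that effectiveness is concluded only from the between-group contrast.

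The cost is a few sentences of text. No participants, data or power are lost: 268 evaluable and 336 randomized remain as they are, and the mixed model and between-group chi-square tests stay in place.
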